***Other study parameters***				
Patient characteristics	Self-reported and Medical Record Data		Age (years), gender (male/female), body mass index (BMI), marital status (living together/alone), comorbidities, Mini-Mental State Examination (MMSE)*, The American Society of Anaesthesiologists Classification of physical health (ASA classification), tumor location (lung, upper GI, HPB, colorectal), stage of cancer (1–4), unintentional weight loss (% over de last 6 months), nutritional intake (% of nutritional requirements) *The MMSE will only be measured when there are doubts about the patient’s cognition. The MMSE is an instrument used for cognitive impairment in the elderly [64]. A low score on the MMSE corresponds to a low cognitive level. A score < 24 (out of 30) is usually considered deviant [65].	T0
Perioperative characteristics	Medical Record Data		Operation technique (open/laparoscopic), pre- or post-treatment with chemotherapy or radiotherapy, length of hospital stay (days)	T1
Self-management Skills	Self-Management Screening tool	SeMaS	The SeMaS is a short tool that can signal potential barriers for self-management that need to be addressed in the dialog with the patients and can facilitate personalized counselling. The following items of the SeMaS will be measured: level of education, experienced burden of disease, digital skills, locus of control, self-efficacy, social support, coping style, anxiety and depression. Based on the outcome factors of the SeMaS tool, the physiotherapist will give specific advice to the patients for the tailored intervention. The SeMaS is validated in patients with chronic condition in primary care [66]. However, this tool contains patient characteristics that are generally important in self-management and the questionnaire is not specific to a particular condition	T0
Treatment fidelity	Audio records		To investigate whether the intervention techniques used in the intervention (MI and SDM) have been implemented properly, some consultations with the physiotherapist and dietician will be audio-recorded. The audio records will be made with professional recording equipment and in no case with a telephone. The consultations will only be recorded if the patient has given his or her specific consent to record their consultations. Researchers trained in the use of MI and SDM will listen to these consultations to determine if the techniques have been used appropriately. The recordings will be made at multiple times during the study as a learning effect of the health professionals is expected. In addition, the number of consultations with the	T1 t/m T5
Treatment adherence	Intervention data		*Treatment adherence* will be measured to determine the extent to which the patients complied with the intervention. The following outcomes will be considered to determine treatment adherence: • Number of days of wearing the PAM sensor • Number of days of for which protein intake is recorded • Number of contact moments with the physiotherapist and dietician	T1 t/m T5
Process evaluation	Focus groups		A qualitative process evaluation will be performed to evaluate the implementation of the intervention in order to identify possible barriers and facilitators for further implementation. Focus groups will be conducted with patients from the intervention group, involved healthcare professionals and members of the research team to evaluate the intervention and implementation process. In addition, user adherence of the smartphone application and web application will be measured during the study	NA
Healthcare use	Self-reported and Medical Record Data		The number of consultations with a healthcare provider will be registered by asking the patients about their use of paramedic consultations in primary care and by screening the Medical Record data. This can be used to determine the difference in healthcare use and costs between the intervention and control group	

T0 = baseline (preoperative), T1 = at hospital discharge, T2 = 1 week after discharge, T3 = 4 weeks after hospital discharge, T4 = 8 weeks after hospital discharge, T5 = 12 weeks after hospital discharge, T6 = 6 months after hospital discharge, NA = not applicable

### Data collection

At baseline, the questionnaires will be sent by the researcher via the OnlinePROMS platform. After registration of the date of hospital discharge, the questionnaires will be automatically sent at 1 week, 4 weeks, 8 weeks, 12 weeks, and 6 months after hospital discharge. To improve the retention rate, patients will receive a reminder automatically after 2 and 5 days.

Standard operating procedures have been established for performing the physical measurements. All research assistants are trained to perform these measurements accurately and consistently. To ensure a higher follow-up rate, researchers have the flexibility to visit patients at home to perform the physical measurements. This approach aims to enhance convenience for participants and increase the likelihood of their continued participation in the study.

### Data management

Data obtained from the medical record and collected during baseline and follow-up measurements will be manually entered into Castor EDC. Castor EDC incorporates protection for data entry and validation to reduce data entry errors, and management features to facilitate audits and data quality assurance. Data from the online questionnaires will be saved at the OnlinePROMS database.

Both databases have been specifically developed to ensure the safeguarding of participant information in accordance with data protection regulations. Participants will be identified solely by a unique patient ID number, ensuring their anonymity. Trial-related documents will be securely stored and restricted to trial staff and authorized personnel only. Data will be anonymized promptly whenever feasible. All essential data that contains identifiable information will be retained for a period of 10 years, while anonymized digital data will be stored indefinitely. The Chief Investigator holds the role of the data manager, overseeing the management and security of the data.

Cleaned data sets will be made available to all Principal Investigators. These data sets will be securely stored on the research drive of Amsterdam UMC, VUmc location, and protected by passwords. Each Project Principal Investigator will have direct access to the data sets from their respective site, and access to data from other sites can be obtained upon request. To ensure confidentiality and privacy, any identifying participant information will be removed from the data sets if possible, when shared with project team members. Access to the full protocol, participant-level dataset and statistical code for non-commercial researchers outside the project team will be available from the corresponding author upon reasonable request.

### Statistical analysis

Missing data will be handled using longitudinal data analysis. The differences in course of recovery between groups, measured with the CAT PROMIS-PF, will be analyzed using linear mixed model analysis, with group as independent variable and the PROMIS-PF at all postoperative measurement points (*T*_1_–*T*_6_) as dependent variable, adjusting for baseline PROMIS-PF (*T*_0_). The primary analysis will be conducted based on the full analysis set according to the intention to treat method.

Descriptive statistics will be calculated for all parameters, include mean, median, standard deviation, standard error of the mean and the interquartile range. In addition, per-protocol analysis will be performed among all participants with sufficient protocol adherence (> 80%). Continuous secondary outcomes are analyzed using linear mixed model, with group as the independent variable and outcome at all postoperative measurement points as dependent variable, adjusting for baseline scores. Dichotomous outcomes are analyzed using generalized mixed model with the same multilevel structure. A mediation analyses will be performed on the longitudinal trial data to determine if the relationship between the intervention and the primary outcome (PROMIS-PF) can be explained by improvement of PA and protein intake.

Qualitative data analysis of the focus groups will be conducted following the steps of thematic analysis by two researchers.

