**Methods:**

In this multicenter single-blinded randomized controlled trial, 161 adult patients scheduled for elective gastrointestinal or lung cancer surgery will be randomly assigned to the intervention or control group. The purpose of the Optimal Physical Recovery After Hospitalization (OPRAH) intervention is to encourage self-management of patients in their functional recovery, by using a smartphone application and corresponding accelerometer in combination with coaching by a physiotherapist and dietician during three months after hospital discharge. Study outcomes will be measured prior to surgery (baseline) and one, four, eight, and twelve weeks and six months after hospital discharge. The primary outcome is recovery in physical functioning six months after surgery, and the most important secondary outcome is physical activity. Other outcomes include lean body mass, muscle mass, protein intake, symptoms, physical performance, self-reported limitations in activities and participation, self-efficacy, hospital readmissions and adverse events.

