Key inclusion and exclusion criteria	Ages eligible for study: ≥ 18 years Sexes eligible for study: both Accepts healthy volunteers: no
	Inclusion criteria: adult patient (≥ 18 years), scheduled for curative intent surgery for gastrointestinal cancer, including esophageal and stomach cancer (upper GI), colorectal and hepato-pancreato-biliary (HPB) cancer, or lung cancer with a planned hospital stay of ≥ 2 nights, able to fill in online questionnaires in Dutch and give informed consent
	Exclusion criteria: pulmonary wedge resection, surgery with open/close procedure, having no access to a mobile device compatible for applications, less than 5 days between inclusion and surgery, patients who are wheelchair dependent, a Mini-Mental State Examination (MMSE) ≤ 24 and already participating in a conflicting study
Study type	Multicenter randomized controlled intervention trial with allocation at level of the individual
	Allocation: randomized
	Primary purpose: treatment
	Phase III trial
Date of first enrolment	June 2022
Target sample size	161
Recruitment status	Recruiting
Primary outcome(s)	Recovery in physical functioning six months after hospital discharge
Key secondary outcomes	Physical activity, lean body mass, pain, fatigue, muscle mass, protein intake, physical performance, patient-specific activity limitations, self-efficacy, participation in social roles and activities, generic quality of life, global perceived effect, hospital readmission and adverse events

However, patients often experience barriers to being physically active after surgery, e.g. due to physical symptoms, such as pain and fatigue, and lack of motivation or social support [13–16]. In addition, previous studies found that many surgical patients were unable to meet their protein requirements after surgery despite the advices of a dietician, e.g. due to a loss of appetite or feelings of worry [17]. Patients emphasize the need for more supportive care interventions after discharge to facilitate return to normal activities after cancer surgery [18, 19]. Therefore, additional support in promoting physical activity and protein intake is needed to improve recovery of physical functioning after surgery in these patients [20].

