### Objective and hypothesis

*Objective:* to evaluate the efficacy of the OPRAH intervention on recovery of physical functioning (compared with usual care) in patients who have undergone elective GI and lung cancer surgery.

*Hypothesis*: The aim of the intervention is to encourage self-management of patients by the use of self-monitoring on physical activity and protein intake. Patients will also be monitored in their recovery of physical activity and protein intake by a physiotherapist and dietician. If this recovery stagnates and goals are not achieved, the physiotherapist or dietician can contact the patient to identify barriers in their recovery. The use of multiple BCTs can help to reduce or eliminate these barriers and to increase the patient’s level of physical activity and protein intake. Higher levels of physical activity and achieving protein requirements are expected to have a positive effect on the recovery in physical functioning after discharge. Therefore, it is hypothesized that patients in the intervention group will have a faster and better recovery in physical functioning during the first 6 months after hospital discharge compared to patients receiving usual care.

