#### Sample size

For the present sample size analysis, a conservative estimate of 0.40 as the between-group effect size on the outcome physical functioning is used. This estimate is based on reported effect sizes on patient-reported outcomes of physical functioning in other studies using technology and coaching on physical activity [26, 27]. Based on alpha = 0.05, power (1 − *β*) = 0.80, a two-sided test for repeated measures with an expected within-subject correlation coefficient of 0.6 and 5 follow-up measurements the minimum number of 67 subjects per group is required, with a total sample size of 134 (see Formula 1). Allowing for a drop-out rate of 20% during the study, this study should include 161 patients.

The most important secondary outcome of this study is objectively measured physical activity. Therefore, a sample size calculation was also made on this outcome measure. Based on the effect sizes found in our recent systematic review and meta-analysis of interventions using activity trackers in patients during or after inpatient stay on the outcome physical activity, an effect size on physical activity of 0.50 is expected [22]. Based on alpha = 0.05, power (1 − beta) = 0.80 and a two-sided test the minimum number of subjects required is *n* = 128 (64 in each group). Allowing a drop-out rate of 20% during the study, a total of 154 patients should be included.

Formula 1:

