### Outcomes

The primary outcome is recovery in physical functioning 6 months after hospital discharge and the most important secondary outcome is physical activity. Other secondary outcomes are lean body mass, pain, fatigue, muscle mass, protein and energy intake, physical performance, patient-specific activity limitations, self-efficacy, participation in social roles and activities, generic quality of life, global perceived effect, hospital readmission and adverse events. See Table 3 for a detailed description of the outcome measures with the corresponding follow-up time points.

**Table 3 Tab3:** Outcome measures

Construct	Measure	Abbrev	Description	Time points

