***Primary outcome***				
Physical functioning	Computer Adaptive Testing (CAT) Dutch-Flemish Patient-Reported Outcome Measure Information System for Physical Functioning	CAT PROMIS-PF	The CAT PROMIS-PF is a digital questionnaire [37]. A CAT is a computer-administered measure in which a computer algorithm is used to select successive items based on responses to previous items. Using a 5-point Likert scale the questionnaire reflects the participant’ functioning in the past 7 days. The items cover a wide range of activities, from activities of daily living to more complex activities [38]. The CAT PROMIS-PF has sufficient psychometric properties in measuring the level of physical function of physiotherapy patients [39] and has been shown to be reliable and sensitive to change in surgical patients [40, 41].	T0, T2, T3, T4, T5, T6

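### The declared primary outcome is physical functioning at six months, but the described primary analysis and the sample size target an effect averaged over all follow-up visits

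*Protocol article*

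**What the plan says.** **Outcome.** The Outcomes section states: "The primary outcome is recovery in physical functioning 6 months after hospital discharge". Table 1 agrees: "Recovery in physical functioning six months after hospital discharge". The abstract counts from a different origin: "The primary outcome is recovery in physical functioning six months after surgery".

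**Hypothesis.** Objective and hypothesis expects "faster and better recovery in physical functioning during the first 6 months after hospital discharge", which covers both speed and level of recovery.

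**Analysis.** The Statistical analysis section says the between-group difference in the course of recovery will be analysed "using linear mixed model analysis, with group as independent variable and the PROMIS-PF at all postoperative measurement points" (given as T1 to T6) "as dependent variable, adjusting for baseline PROMIS-PF". It mentions no visit term, no group-by-visit term and no six-month contrast.

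**Sample size.** The calculation uses an effect size of 0.40, alpha 0.05, power 0.80 and "a two-sided test for repeated measures with an expected within-subject correlation coefficient of 0.6 and 5 follow-up measurements". It gives 67 per group, 134 in total, and 161 after an allowance for drop-out.

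**Visits.** Table 3 lists PROMIS-PF at "T0, T2, T3, T4, T5, T6", so there are five follow-ups and none at T1.

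**The concern.** The outcome is tied to one visit, while the analysis described for it uses all visits and reports one group effect. Such an effect does not isolate six months. Nor can it show that the groups recover along different courses, because that needs the group difference to vary with visit.

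This matters because of the trial's timing. Under Intervention description and procedures, remote coaching runs for three months after discharge, and T6 falls three months later. A benefit that is present during coaching and gone by T6 could make the averaged test significant, and the result would then be reported against a six-month outcome. A benefit that builds up slowly would be diluted by the week 1 and week 4 visits.

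**Working it through.** **Inputs.** From the Sample size section: d = 0.40, two-sided alpha 0.05, power 0.80, within-subject correlation ρ = 0.6, m = 5 follow-ups. Variances are in SD² units. *Assumption:* where baseline adjustment is used, the baseline-to-follow-up correlation r is also taken as 0.6 and then varied. The protocol gives no separate value for it.

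**1. Reproduce the 67.** Formula 1 is not legible in the available text, so it is identified by its result. For the mean of m follow-ups, n per group = 2(1.960 + 0.842)² × [1 + (m − 1)ρ]/m ÷ d².

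- The variance factor is (1 + 4 × 0.6)/5 = 0.68.
- n = 2 × 7.849 × 0.68/0.16 = 66.7, rounded up to 67. This matches.

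The alternatives do not match:

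- single visit, unadjusted: 2 × 7.849/0.16 = 98.1, so 99;
- single visit, baseline-adjusted (variance 1 − 0.6² = 0.64): 62.8, so 63;
- five-visit mean, baseline-adjusted (variance 0.68 − 0.36 = 0.32): 31.4, so 32.

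The trial is therefore sized for the unadjusted five-visit mean.

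**2. What the group coefficient estimates.** The generalised least squares weights over visits are proportional to V⁻¹1. With complete data:

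- equal correlations of 0.6 give 0.20 at each visit;
- first-order autoregressive correlation of 0.6 with equal steps (an assumption) gives 0.31 at T2 and T6 and 0.125 at each visit between.

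Either way it is a weighted average. A visit main effect alone would not change this. Only a group-by-visit term separates T6.

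**3. How far the targets can part.** Power = Φ(√(n d²/(2v)) − 1.96), with n = 67, v = 0.32 for the adjusted average and v = 0.64 for adjusted T6. The effect patterns are assumed.

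| Effect at T2, T3, T4, T5, T6 (SD) | Average | Power, average | T6 effect | Power, T6 |
|---|---|---|---|---|
| 0.4 throughout | 0.40 | 98% | 0.40 | 82% |
| 0, 0.1, 0.2, 0.3, 0.4 | 0.20 | Φ(2.05 − 1.96) = 53% | 0.40 | 82% |
| 0.3, 0.4, 0.4, 0.4, 0 | 0.30 | Φ(3.07 − 1.96) = 87% | 0 | 5% (alpha) |

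Simulation gives the same picture (160 patients, random-intercept model without visit, recovery curve rising 1 SD, 20% drop-out). The fading pattern is significant in 90 to 92% of trials, against 5 to 5.5% for the T6 contrast. The rising pattern is estimated at 0.16 to 0.19 with 44 to 50% power, against 0.40 to 0.41 with 81 to 84% for T6.

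**4. Power if T6 is primary.** Here v = 1 − r² and d = 0.40. The 64 per arm column reflects 161 × 0.8 = 128.8 completers.

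| Baseline-to-T6 correlation r | 67 per arm | 64 per arm |
|---|---|---|
| 0.6 | 82% | 81% |
| 0.5 | 76% | 74% |
| 0.4 | 71% | 69% |
| unadjusted | 64% | 62% |

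**The case against.** The article condenses a fuller protocol and gives the model in one sentence. Fixed time effects, covariance structure and contrasts are commonly left to an analysis plan, and the same section speaks of longitudinal analysis and of the course of recovery. A reader might infer that the model excludes time. The text does not establish that, since silence in a condensed article is not exclusion. This part of the objection stands. It does not remove the mismatch: with visit added as a main effect the group effect is still an average, and with an interaction added it remains unsaid which effect is the primary test.

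The hypothesis, the sample size and the analysis all concern recovery over the whole follow-up, so the six-month label could be the part that is out of line. This also stands. It makes redefining the outcome a legitimate repair, and the choice belongs to the trial team.

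The effect patterns used above are chosen, and under a constant effect the targets coincide. That is right: they show what could happen and are not evidence about this trial.

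A reader might also infer that unequal drop-out would seriously bias a model without visit. Simulation gives a bias of about 0.04 to 0.05 SD and 7 to 8% rejections under no effect, but only with an assumed 10% against 30% split and a 1 SD recovery curve. The protocol gives only 20% overall. This is a secondary reason to include visit.

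**Conclusion.** The point holds as a mismatch between what is declared and what is described. The primary outcome is PROMIS-PF at six months after discharge, whereas the described analysis and the sample size target an average over T2 to T6. Followed as written, the plan would give its verdict on a quantity other than its declared primary outcome, so this must be settled before unblinding.

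The size of the discrepancy depends on how the effect changes over visits. It is nil under a constant effect and large under the fading or rising patterns shown. The exact weight on T6 depends on the covariance structure and on missing data.

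A reader might conclude that moving to T6 needs no additional patients. The documents do not support that without qualification. It relies on a baseline-to-T6 correlation near 0.6, and the protocol gives 0.6 only as a general within-subject value. Baseline precedes major surgery and T6 comes more than six months later, so a lower value is plausible.

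Two wording slips are minor. T1 is listed among the PROMIS-PF outcome visits although PROMIS-PF is not collected then, and the abstract counts six months from surgery.

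**What to change.** Choose one target and make the outcome, model and sample size agree on it before unblinding.

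- **If six months is intended:** fit PROMIS-PF at T2 to T6 with categorical visit, group, group-by-visit and baseline PROMIS-PF. Name the T6 group contrast as the single primary test and report the T2 to T6 average as secondary. Restate the power for T6 over a range of baseline-to-T6 correlations.
- **If the average is intended:** openly redefine the primary outcome as the T2 to T6 average, matching the model and the sample size, and report the T6 contrast as secondary. Visit should be in the model here too.

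In both cases, change the PROMIS-PF outcome visits to T2 to T6 and align the abstract with six months after discharge.

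The cost is a change of wording in the protocol and analysis plan, with no new data. The downside of choosing T6 is lost precision: about 82% power against 98% for the adjusted average, under a constant effect of 0.40, correlation 0.6 and 67 per arm. The downside of choosing the average is a visible change to the declared primary outcome, and no primary claim specific to six months.
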